## Methods

### Study Design

To test our hypothesis and achieve our objectives, we shall compare adherence to the first prescribed antipsychotic medication and pragmatic clinical and functional outcomes between 2 cohorts of patients with first-episode psychosis. One cohort will comprise patients treated before the implementation of an early intervention in psychosis model of personalized precision psychiatry, including pharmacogenetics, and the other will comprise patients treated under this new model. In addition, we shall compare the pharmacogenetic profiles and possible phenocopies (variations of phenotypes produced environmentally, eg, due to polypharmacy, rather than genetically) between these patients with first-episode psychosis and a national sample of patients with longer-term psychotic disorders or other mental health conditions to evaluate potential implications for clinical management at different stages of a psychotic illness and across mental disorders.

### Participants

A total of 300 patients will be included in this project. We shall include 2 different cohorts. Cohort 1 will be a prospective sample of patients with first-episode psychosis referred over 18 months to the new early intervention in psychosis program of personalized precision psychiatry (PRINT) at CAUSA. Cohort 2 will be a retrospective, consecutive (in reverse chronological order as registered in the CAUSA electronic health records) sample of patients who experienced a first episode of psychosis before the implementation of PRINT.

Inclusion and exclusion criteria for both cohorts will be aligned with the PRINT program referral acceptance criteria, which are predominantly inclusive.

Inclusion criteria are as follows: patients (1) with a diagnosis of first-episode psychosis, either nonaffective or affective; (2) aged 12 to 35 years; and (3) followed by clinical services for at least 1 year or earlier if there was evidence of antipsychotic treatment discontinuation (see the Outcome Measures section). In addition, patients in cohort 1 or their family or legal representatives will have to provide written consent to take part in the CLUMP project, including pharmacogenetics analysis (see the Ethical Considerations section). For patients in retrospective cohort 2, this will not be an inclusion criterion, but all of them will be approached by our research team seeking their consent to obtain their pharmacogenetic profile for research purposes.

Exclusion criteria are as follows: patients (1) with first-episode psychosis due to organic causes, for example, brain diseases such as Huntington or Parkinson disease, HIV, syphilis, dementia, brain tumors or cysts, or brain injury; (2) with moderate to severe intellectual disability; and (3) who spent (cohort 2) or plan to reside during (cohort 1) most of the 1-year follow-up period in a locality out of the PRINT program’s catchment area.

For additional comparative purposes, we shall analyze the environmental, clinical, and pharmacogenetic information of patients with psychotic disorders of more than 5 years of evolution or with other mental disorders whose data are currently stored and have been ethically approved for research use in our unit of pharmacogenetics and precision medicine at the HUS.

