Cohort 2 will have received standard care provided by mental health services before the PRINT program implementation, specifically by mental health professionals working in generic community mental health teams that offer assessment and treatment to people who reside in their geographical catchment areas and experience a wide range of mental disorders, not only psychotic disorders.

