### Outcome Measures

#### Primary Outcome Measure

The primary outcome to measure treatment adherence will be all-cause discontinuation of the initially prescribed antipsychotic medication following the patient’s or treating clinician’s decision. All-cause discontinuation rates in the CLUMP project will be defined by all-cause discontinuation proportions during the 1-year follow-up and the mean time to such discontinuation.

For cohort 1, the 1-year follow-up period will start when an antipsychotic medication is prescribed taking into consideration the pharmacogenetics advice emerging from the 5SPM method. For cohort 2, follow-up would begin on the date when the first antipsychotic medication was prescribed. For both cohorts, the first prescribed antipsychotic will be the initially prescribed antipsychotic drug for maintenance treatment, not only for short-term use to control psychomotor agitation. In addition, in accordance with existing scientific consensus, the discontinuation date will be defined as the first day of a 2-week or longer interruption of the first prescribed antipsychotic. In cohort 2, treatment discontinuation dates will be determined by examining clinical records. Where only approximate dates are available, the first, middle, or final day of the month will be used as best estimates. In cases in which cross-titration of medication took place, the date of discontinuation will be the first day of the cross-tapering process.

All-cause discontinuation will also be stratified by 4 reasons: insufficient efficacy, adverse events, lack of adherence, and other. Insufficient efficacy will be established at the treating clinician’s judgment only after at least 3 weeks of treatment. If more than one reason for discontinuation was present, we shall select one by applying the ranking order as stated previously.

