### Effect and Sample Size

We conducted a power calculation for the main outcome: the proportion of patients with first-episode psychosis who, by their treating clinician’s or their own decision, discontinue, for any reason, the first prescribed antipsychotic medication within 1 year. As stated previously, recent research studies, mostly carried out in early intervention settings, concur that 40% of patients with first-episode psychosis experience first prescribed antipsychotic drug discontinuation during the first year following treatment initiation [7,8]. This proportion may be even higher in patients receiving mainstream psychiatric care, such as our cohort 2. Considering the expectations behind the use of personalized precision medicine, PRINT should aim to reduce discontinuation rates to 10%. Therefore, for a power of 80% with (1) a significance level of .05 (2-sided), (2) all-cause discontinuation rate in cohort 1 (intervention) of 0.4, (3) all-cause discontinuation rate in cohort 2 (treatment as usual) of 0.1, and (4) an expected dropout or loss to follow-up rate of 0.2, our calculations would require a sample size of at least 38 patients in each cohort. We used the R statistical software *pwr* package for this calculation (version 4.4.2 for Windows; R Foundation for Statistical Computing).

In CAUSA, we have found an administrative incidence of 50 new patients aged 12 to 35 years every year. Thus, we would expect at least 75 patients eligible to be recruited for cohort 1 over 18 months. Using a conservative approach, if 25 patients (approximately 35%) do not agree to take part, we would still enroll 50 patients. This would be in addition to another 50 patients in our retrospective cohort 2 and pharmacogenetic data currently available at CAUSA from 100 patients with psychotic disorders of more than 5 years of evolution and another 100 patients with other mental disorders that we shall use for further comparative purposes, as outlined previously. This all accounts for a total of 300 participants contributing to this project.

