### Statistical Analysis

Comparisons of the main outcome (ie, discontinuation rates) will be carried out using the chi-square test. Kaplan-Meier survival curves and multivariate log rank tests will be used to assess time to all-cause antipsychotic discontinuation. For these analyses, patients will be followed up on for a year, from antipsychotic treatment initiation until discontinuation. Thus, we shall censor survival time by the end of the 1-year observation period or before such date if there is enough evidence of antipsychotic discontinuation. We shall describe and compare sociodemographic information and clinical and functional outcomes within and between groups. Means and SDs will be used to describe quantitative variables. We shall use the chi-square test or Fisher exact test for categorical variables and Mann-Whitney *U* test for continuous variables, among others. Data analyses will be conducted using the R statistical software (version 4.4.2 for Windows).

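### Cohort 2 is sampled most recent first with no gap before PRINT, so most control follow-up years run past the launch and the pre-PRINT comparator is not secured

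*Protocol article*

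**What the plan says.** All references are to the protocol article.

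- **Sampling rule (Participants).** "Cohort 2 will be a retrospective, consecutive (in reverse chronological order as registered in the CAUSA electronic health records) sample of patients". The sole calendar limit attaches to the episode and takes in those "who experienced a first episode of psychosis before the implementation of PRINT". No interval between the index prescription and the PRINT launch is required.
- **Comparator (Clinical Management and Pharmacogenetics Analysis).** "Cohort 2 will have received standard care provided by mental health services before the PRINT program implementation". Study Design likewise describes this cohort as treated before the new model came in.
- **Rate and size (Effect and Sample Size).** "we have found an administrative incidence of 50 new patients aged 12 to 35 years every year". The article treats that rate as eligible: "we would expect at least 75 patients eligible to be recruited for cohort 1 over 18 months". It plans "another 50 patients in our retrospective cohort 2".
- **Follow-up.** "For cohort 2, follow-up would begin on the date when the first antipsychotic medication was prescribed" (Primary Outcome Measure), and "patients will be followed up on for a year, from antipsychotic treatment initiation until discontinuation" (Statistical Analysis). Economic Evaluation uses a 1-year horizon from antipsychotic initiation in both cohorts.

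The article gives neither the PRINT launch date nor a rule on whether patients already in care could move into PRINT.

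**The concern.** The sampling rule looks at when the episode occurred. The comparator is defined by the care received over the following year. Sampling backwards from launch with no gap picks the controls whose follow-up year overlaps PRINT the most.

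This matters because cohort 2 is the only comparator for the primary outcome. Controls remain in the catchment area for most of the year, and their criteria are aligned with PRINT's referral criteria. The third inclusion criterion asks only for follow-up by clinical services, so a control who moved to PRINT would stay eligible. If some did move, the control arm would mix standard care with the care under test. If they were later left out because they no longer fit the comparator, the exclusion would depend on an event after the index date.

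**Working it through.** **1. The plan's own figures reproduce.**
- Accrual: 50 per year × 1.5 years = 75 eligible, as stated.
- Sample size, with the arcsine effect size used by the *pwr* package: h = 2·asin(√0.4) − 2·asin(√0.1) = 0.726. Then n = 2·((1.960 + 0.842)/0.726)² = 29.8, rounded up to 30, and 30/0.8 = 37.5, rounded up to 38, as stated.
- I take 40% as the usual-care risk and 10% as the PRINT target, following the rationale in that section. Its numbered list attaches the two rates to the opposite cohorts.

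**2. Calendar overlap.** Space the controls evenly backwards from launch at rate r per year. The sampling window is 50/r years, and a control crosses launch if the index date is less than 1 year before it.

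| Qualifying rate per year | Window | Controls crossing launch | Mean time after launch, all 50 |
|---|---|---|---|
| 50 (stated) | 12 months | 50 of 50 | 6.0 months |
| 40 (assumed: 20% do not qualify) | 15 months | 40 of 50 | 4.8 months |
| 30 (assumed) | 20 months | 30 of 50 | 3.6 months |

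With random (Poisson) arrivals at 50 per year, the expected number crossing is 47 of 50 (95% range 37 to 50).

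**3. Overlap that counts for the primary outcome.** Time on the first antipsychotic ends at discontinuation, so step 2 overstates the overlap for this outcome. Assume a constant hazard with 40% risk at 1 year: λ = −ln 0.6 = 0.511. At 50 per year:
- On the first drug at launch: 50 × 0.4/λ = 50 × 0.783 = 39 of 50 (78%).
- Share of at-risk time after launch: [(0.783 − 0.6)/λ] / 0.783 = 0.358/0.783 = 46%.
- Expected discontinuations after launch: 50 × (0.783 − 0.6) = 9 of 20.

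At 40 per year these become 31 of 50, 37% and 7 of 20. The cost horizon is not cut short by discontinuation, so step 2 applies to it in full.

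**4. What exposure could do (illustration only).** The transfer rate is not in the article.
- *PRINT lowers control discontinuation.* Suppose every control moved at launch and then had the hazard behind the 10% target, −ln 0.9 = 0.105. Averaged over index dates at 50 per year, the proportion not discontinuing is 0.6 × (1.5 − 1)/ln 1.5 = 0.740, so control risk is 26%. Exact power of the uncorrected chi-square test against 10%, with 40 evaluable per cohort, falls from 90% to 48%. If half transfer, risk is 33% and power 73%; if a quarter, 36.5% and 83%. At 40 per year with full transfer, risk is 0.8 × 26% + 0.2 × 40% = 29% and power 59%.
- *PRINT raises control discontinuation.* Step 4 of the 5SPM method may introduce or change drug treatment. Under Primary Outcome Measure a clinician's change of the first antipsychotic is a discontinuation. Transfer could then push the control rate up and widen the contrast.
- *Transferred controls are dropped.* About 11 of 50 stop before launch and are kept. If a quarter of the 39 still on drug are removed, the observed rate is (10.85 + 0.75 × 9.15)/(50 − 9.79) = 44% instead of 40%; if half, 51%.

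**The case against.** A reader might infer that the controls were in fact treated in PRINT and that power drops to about 48%. The article does not support that. It shows calendar overlap and does not say that existing patients of the generic teams moved. PRINT's steps are aimed at the time a first episode is identified, which suggests new presentations. The 26% and 48% figures need every control to transfer at launch and to take on the full target hazard. Yet the planned benefit comes largely from choosing the first antipsychotic with pharmacogenetic advice, and these controls had already started theirs. A drug change on entry would move the rate the other way. These points stand, and they rule out a claim about direction or a headline power loss.

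The illustration also weakens under milder assumptions. The inclusion rule admits only controls with a full year or a discontinuation, so all 50 may be evaluable. With 50 controls against 40 PRINT patients, 40 qualifying per year and half transferring, power is about 81%. This stands too. Nor does the article propose dropping transferred controls; that is only one way someone might later reconcile the texts.

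It can also be said that the article already defines the comparator as pre-PRINT care, and that the extraction window belongs to the full protocol. This stands only in part. The article does state a sampling rule, and at its own accrual rate that rule does not deliver the comparator described. That is a mismatch between two stated things, and it has to be settled before records are extracted.

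Finally, recent controls limit secular differences in drugs and practice. That is a real advantage of the present rule and the main cost of changing it.

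**Conclusion.** The point holds as a gap between the sampling rule and the stated comparator. At the stated 50 patients per year, the nominal follow-up year of essentially every control runs past launch, and at 40 qualifying per year four in five do. For the primary outcome the overlap is smaller: about 78% are still on the first drug at launch and about 46% of at-risk time falls after it, given even accrual, a constant hazard and 40% risk.

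Exposure of controls to PRINT is possible but not shown, and its direction is uncertain. The 26% control risk and 48% power are an illustrative upper bound on dilution under full transfer, not an estimate. If the intention was that the whole year precede PRINT, the sampling would have to start at least 12 months before launch, and the article does not say so. The change is worth making because it removes the question by design at little cost.

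**What to change.** 1. State the PRINT launch date, and whether patients already in care could enter PRINT.
2. Define cohort 2 as consecutive patients, in reverse chronological order, whose first maintenance antipsychotic was prescribed at least 12 months before that date. The whole follow-up year, including the secondary outcomes and the cost horizon, is then pre-PRINT. At 50 per year the window runs from about 24 to 12 months before launch; at 40 per year, from about 27 to 12 months.
3. As a sensitivity analysis, add the more recent controls to the time-to-event analysis and censor them at launch. Launch is a fixed calendar date, so this avoids selecting on what happened to the individual patient. It does not carry over to the chi-square comparison, which needs the full year.

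Cost: cohort 2 is retrospective, so the change only moves the record-extraction window. The downside is one more year of calendar distance between the cohorts; the sensitivity analysis helps show whether that matters.

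### Inclusion criterion 3 makes eligibility depend on the primary outcome, so patients lost while still on their first antipsychotic drop out of the denominator

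*Protocol article*

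**What the plan says.** All of the text at issue is in the Methods of the protocol article.

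- **Participants, inclusion criterion 3:** patients must be "followed by clinical services for at least 1 year or earlier if there was evidence of antipsychotic treatment discontinuation". The criterion refers the reader to the Outcome Measures section.
- **Participants, scope:** one set of criteria serves both groups: "Inclusion and exclusion criteria for both cohorts will be aligned with the PRINT program referral acceptance criteria". Cohort 1 is prospective. Cohort 2 is a consecutive series taken backwards in time from the electronic records.
- **Primary Outcome Measure:** the outcome is "all-cause discontinuation of the initially prescribed antipsychotic medication following the patient’s or treating clinician’s decision", summarised as "all-cause discontinuation proportions during the 1-year follow-up and the mean time to such discontinuation".
- **Effect and Sample Size:** the calculation allows for "an expected dropout or loss to follow-up rate of 0.2" and arrives at 38 per cohort, with 50 per cohort planned.
- **Statistical Analysis:** "Comparisons of the main outcome (ie, discontinuation rates) will be carried out using the chi-square test". For the Kaplan-Meier and log-rank analyses the plan is to "censor survival time by the end of the 1-year observation period or before such date if there is enough evidence of antipsychotic discontinuation". No other end of observation is given.
- **Participants, exclusion criterion 3:** this removes patients "who spent (cohort 2) or plan to reside during (cohort 1) most of the 1-year follow-up period" outside the catchment area.

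The Limitations section does not mention selection by completeness of follow-up.

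**The concern.** Criterion 3 has two branches: a full year under clinical services, or less than a year with evidence of discontinuation. The second branch is the primary event itself. A patient lost to services at month 5 while still taking the first drug satisfies neither branch and is not eligible, whereas a patient who stopped at month 5 is. The primary proportion is therefore events divided by events plus one-year completers, not events among those who started treatment.

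In cohort 2 the rule can be applied exactly as written, because the records already show who stayed. Working back to 50 patients while passing over those lost on treatment fills their places with earlier patients whose outcome is known. In cohort 1 the rule cannot be applied at enrolment, so on the literal wording it works as an exclusion after enrolment.

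What is at stake is the between-cohort comparison. Cohort 1 is a consented group followed prospectively in a dedicated programme. Cohort 2 was seen by generic teams, and its discontinuation dates are read from clinical records. Equal loss in the two, which is needed for the distortion to be similar, cannot be taken for granted.

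**Working it through.** **The plan's own figure.** Inputs from Effect and Sample Size: 0.4 and 0.1, two-sided 0.05, power 80%, loss 0.2. With the arcsine effect size used by the pwr package, h = 2·asin(√0.4) − 2·asin(√0.1) = 0.726, and n = 2 × ((1.960 + 0.842)/0.726)² = 29.8, rounded up to 30. Then 30/(1 − 0.2) = 37.5, rounded up to 38. The stated 38 is reproduced, and the 20% allowance is already in it.

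**What criterion 3 estimates.** Assume constant hazards and loss independent of discontinuation. For a true 12-month risk p and a net loss L (the probability of being lost by 12 months if nobody discontinued):

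- λ = −ln(1 − p) and μ = −ln(1 − L)
- share discontinuing first, D = λ/(λ + μ) × (1 − e^−(λ+μ))
- share completing the year on the drug, S = e^−(λ+μ) = (1 − p)(1 − L)
- proportion under criterion 3 = D/(D + S)

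For p = 0.40:

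| Net loss L | D | S | Lost on drug | D/(D + S) |
|---|---|---|---|---|
| 5% | 39.1% | 57.0% | 3.9% | 40.7% |
| 20% | 36.2% | 48.0% | 15.8% | 43.0% |
| 40% | 32.0% | 36.0% | 32.0% | 47.1% |

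Worked line for 20%: λ = 0.511, μ = 0.223, D = 0.511/0.734 × 0.52 = 0.362, S = 0.6 × 0.8 = 0.48, and 0.362/0.842 = 0.430.

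If 20% instead means the share actually observed to be lost while on the drug, then μ = 0.291, D = 35.1%, S = 44.9%, and the proportion is 43.9%. The conclusion is the same.

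**Effect on the comparison.** Only the single figure of 20% comes from the protocol; all cohort-specific rates below are assumptions.

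- Equal 20% net loss, true risk 40% in both cohorts: 43.0% versus 43.0%, so no false difference.
- Equal 20% net loss, true risks 40% and 10%: 43.0% and 11.1%, a difference of 31.9 points instead of 30.
- True risk 40% in both, net loss 10% in cohort 1 and 30% in cohort 2: 41.4% versus 44.8%, a false 3.5-point benefit.
- True risk 40% in both, net loss 5% in cohort 1 and 40% in cohort 2: 40.7% versus 47.1%, a false 6.4-point benefit. With 50 per cohort the standard error is √(2 × 0.439 × 0.561/50) = 0.099, so the shift is 0.64 standard errors, and the two-sided false-positive rate rises from 5% to about 10%.
- If cohort 1 has the greater loss, the sign reverses.

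**Informative loss.** Suppose the true risk in cohort 2 is 50%, and 10% or 20% of that cohort left services and stopped the drug with no record of it. Criterion 3 deletes them, giving (0.5 − 0.1)/0.9 = 44.4% or (0.5 − 0.2)/0.8 = 37.5%. Here cohort 2 looks better than it was, and the bias runs against the programme.

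**The case against.** The best defence concerns cohort 1. Effect and Sample Size goes from 75 expected eligible patients to 50 enrolled by subtracting only refusals, with nothing removed for incomplete follow-up. Criteria tied to referral acceptance must also be judged at referral. Both points fit a reading in which cohort 1 enters at consent and criterion 3 merely describes the observation window. That reading is possible, but the text does not state it. It also leaves cohort 2 filtered on completion or event while cohort 1 is not, so the cohorts would be selected by different rules.

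Four stronger readings are tempting, and the document does not support them:

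- *The criterion flatly contradicts the 20% loss allowance.* The two sit badly together, but the inflation can be read as the usual allowance for enrolled patients who turn out not to be evaluable.
- *The residence exclusion has the same flaw.* It does not select on the outcome, and planned residence can be judged at baseline in cohort 1. What remains is that cohort 2 uses actual later residence, so the rule differs by cohort. That is a separate and lesser point.
- *The survival analysis has no censored patients.* Everyone still on the drug at one year is censored administratively. Only censoring at earlier loss is missing.
- *The bias favours the programme.* Its direction depends on which cohort loses more patients and whether those lost had already stopped.

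It is also fair to say that, on the protocol's own single loss figure, the distortion is modest beside the planned 30-point difference.

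**Conclusion.** The concern holds as a selection problem in the eligibility rule. It is not an error in the sample size, which reproduces. A patient followed for under a year qualifies only through the primary event, and nothing elsewhere in the article brings back those lost on treatment. This is certain for cohort 2. For cohort 1 it follows from the literal wording, and the alternative reading exchanges it for unequal selection between cohorts.

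The size is about 3 points within a cohort at 40% true risk and 20% net loss. The effect on the comparison is nil under equal loss and equal risks, a few points under unequal loss, and about 6 at the assumed extreme of 40% versus 5%. These figures rest on constant hazards and independent loss. With unrecorded stopping the sign is unknown. A larger sample would not remove the bias. Because the rule fixes who is in the primary denominator, it should be corrected in the protocol and not left to the analysis plan.

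**What to change.** 1. Replace inclusion criterion 3 by facts known at the index prescription, worded identically for both cohorts, and keep every eligible patient who starts a first antipsychotic.
2. In the Kaplan-Meier analysis already planned, censor patients lost to services at the last documented contact on the drug.
3. Report the 12-month Kaplan-Meier discontinuation risk by cohort and the difference with a 95% CI, alongside the chi-square comparison, and state how the chi-square counts patients lost on treatment.
4. Add a sensitivity analysis counting loss as discontinuation. Censoring alone does not deal with informative loss. In the 40% risk, 20% net loss example, this analysis gives 36.2% + 15.8% = 52.0%, an upper limit for that cohort.
5. As a lesser, separate change, apply the residence criterion in the same way in both cohorts, using address at the index date.

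The cost is slightly wider intervals, a last-contact date to extract from records that are already being reviewed for discontinuation dates, and a protocol amendment while recruitment is under way. The required 38 per cohort does not change, because the 20% allowance is already included.

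### Inclusion criterion 3 makes entry to the primary denominator depend on the primary outcome, with certainty in retrospective cohort 2 and, if applied literally, in cohort 1 too

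*Protocol article*

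**What the plan says.** In the protocol article, Participants, one list of criteria serves both groups: "Inclusion and exclusion criteria for both cohorts will be aligned with the PRINT program referral acceptance criteria". The third inclusion criterion is to be "followed by clinical services for at least 1 year or earlier if there was evidence of antipsychotic treatment discontinuation". Cohort 2 is a "retrospective, consecutive (in reverse chronological order as registered in the CAUSA electronic health records) sample of patients", so the criterion is applied to it when a year of history is already on file.

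Under Primary Outcome Measure, the outcome is defined by "all-cause discontinuation proportions during the 1-year follow-up and the mean time to such discontinuation". For the historical patients, "In cohort 2, treatment discontinuation dates will be determined by examining clinical records". No rule covers a patient whose drug status becomes unknown.

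Under Statistical Analysis, "Comparisons of the main outcome (ie, discontinuation rates) will be carried out using the chi-square test". For the survival analysis, "we shall censor survival time by the end of the 1-year observation period", or sooner where discontinuation is evident. Loss to services is not named as a reason for censoring. Effect and Sample Size allows for "an expected dropout or loss to follow-up rate of 0.2".

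**The concern.** Take two patients who both leave services at month 5. One has a documented stop and is eligible, counting as an event. The other was still on the drug when last seen, or stopped without any record of it, and is not eligible. Events before departure are kept, while non-events and unrecorded events before departure are deleted. Each cohort's proportion is then conditional on the outcome it is meant to estimate.

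This matters because the comparison is not randomised and the two services probably keep contact differently. Cohort 1 is treated in a dedicated early intervention programme, a model that the Background describes as assertive. Cohort 2 was treated by generic community teams. Leaving care and stopping the drug are also plausibly linked: lack of adherence is one of the four listed reasons for discontinuation. If the deletion is unequal, it enters both the chi-square and the log-rank comparison. In cohort 2, sampled backwards through the records, leavers can be passed over without anyone counting them.

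**Working it through.** **1. The plan's own figure.** Inputs from Effect and Sample Size: rates 0.4 and 0.1, two-sided 0.05, power 80%, loss 0.2, R package pwr (arcsine effect size).
- h = 2·asin(√0.4) − 2·asin(√0.1) = 0.726
- n = 2·[(1.960 + 0.842)/h]² = 29.8, rounded up to 30
- 30/0.8 = 37.5, rounded up to 38

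The stated 38 per cohort is reproduced exactly.

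**2. Loss unrelated to stopping (assumption).** Let p be the true 1-year discontinuation proportion and L the proportion who would leave services within the year if nothing else intervened. Assume constant, independent hazards λ = −ln(1 − p) and μ = −ln(1 − L).
- Stop seen before loss: D = λ/(λ + μ) · [1 − (1 − p)(1 − L)]
- Full year on drug: C = (1 − p)(1 − L)
- Proportion analysed under criterion 3: D/(D + C)

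Example, p = 0.40 and L = 0.20: λ = 0.511, μ = 0.223, D = 0.362, C = 0.480, so D/(D + C) = 0.362/0.842 = 0.430. The remaining 15.8% of patients are deleted.

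| Loss L | True 40% is analysed as | True 10% is analysed as |
|---|---|---|
| 10% | 41.4% | 10.5% |
| 20% | 43.0% | 11.1% |
| 30% | 44.8% | 11.8% |
| 40% | 47.1% | 12.7% |

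Only the 20% figure comes from the article; the other loss rates are assumptions. With a true 40% in both cohorts:
- 20% loss in both: 43.0% against 43.0%, no false difference
- 10% against 30%: 44.8 − 41.4, about 3.5 points before rounding
- 10% against 40%: 47.1 − 41.4 = 5.7 points

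At the planning rates with 20% loss in both, a 30-point difference becomes 43.0 − 11.1 = 31.9 points.

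**3. Leavers are all unrecorded stoppers (extreme assumption).** Suppose a share L of all patients leaves this way. With a true 40%, the analysed proportion is (0.40 − L)/(1 − L).
- L = 5%: 0.35/0.95 = 36.8%
- L = 20%: 0.20/0.80 = 25.0%

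Two cohorts with the same true rate would appear about 12 points apart, and the cohort with more loss would look better. The direction is opposite to step 2.

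**4. Bounds at the planned size.** Take 50 per cohort and 20% loss: 40 classifiable and 10 unknown in each. Chi-square without continuity correction:

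| Handling of the 10 unknown per cohort | Counts | p |
|---|---|---|
| Deleted | 4/40 v 16/40 | 0.002 |
| All continuing | 4/50 v 16/50 | 0.003 |
| All discontinued | 14/50 v 26/50 | 0.014 |
| Discontinued in the low-rate cohort only | 14/50 v 16/50 | 0.66 |

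An observed 40% is compatible with 16/50 = 32% to 26/50 = 52% of all patients. An observed 10% is compatible with 4/50 = 8% to 14/50 = 28%.

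**5. Does censoring alone repair it?** Suppose 40% recorded stops among those retained, all leavers in fact stopping, and loss of 5% against 20%. The true rates are 0.05 + 0.95 × 0.40 = 43% and 0.20 + 0.80 × 0.40 = 52%. Criterion 3 yields 40% against 40%. Kaplan-Meier with leavers censored at times spread evenly over the year yields about 39% against 36%, which is the wrong direction. Censoring helps when loss is uninformative, as in step 2. It does not help here.

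**The case against.** Four points can fairly be made for the plan.

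- **The loss allowance.** A reader might infer that a 20% loss allowance contradicts a criterion that leaves no lost patients in the analysis. It does not. Enrolling 38, finding up to a fifth not evaluable and analysing 30 is consistent. This point stands, and no contradiction is claimed.
- **Cohort 1.** A reader might infer that the defect is equally certain in both cohorts. The text does not support that. Cohort 1 is prospective, the criterion points to the Outcome Measures section, and the catchment exclusion is worded prospectively for that cohort. The authors may have meant a follow-up definition there. Against this, the text still lists it as an inclusion criterion and gives no other handling, so the wording needs settling.
- **Size.** The article gives a single loss rate with no split by cohort. With equal loss the false difference under step 2 is nil. Even 3.5 to 5.7 points is below the standard error of the difference, √(2 × 0.4 × 0.6/50) = 9.8 points. Step 3 is a worst case, since any interruption of 2 weeks or longer counts and approximate dates are accepted, so some leavers would be kept as events. All of this stands as a limit on size. It does not make the entry rule sound.
- **Brevity of the article.** An unseen analysis plan could supply sensitivity analyses. It could not restore patients whom a printed eligibility rule never admitted. The catchment exclusion would remove only some of them on other grounds.

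**Conclusion.** The point holds as an eligibility defect. Criterion 3 lets the primary outcome decide who enters the primary denominator, and nothing in Primary Outcome Measure, Effect and Sample Size or Statistical Analysis reverses it. It is firm for cohort 2 and conditional on a literal reading for cohort 1.

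A reader might infer that the rule manufactures a benefit for the new programme. The article does not support any direction. Loss unrelated to stopping inflates the proportion more in the cohort with more loss, and unrecorded stopping deflates it there. The false difference ranges from zero with equal loss to 3.5 to 5.7 points with independent loss of 10% against 30% to 40%. It reaches about 12 points the other way in the extreme case of 5% against 20% unrecorded stoppers. All of these except the 20% rest on assumed loss rates. The practical harm is that the rule removes the very patients needed to tell these cases apart.

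**What to change.** 1. Delete criterion 3 as an eligibility rule in both cohorts. Define eligibility by facts known at the index maintenance antipsychotic prescription, and keep every eligible patient.
2. Amend Statistical Analysis so that patients lost without a documented stop are censored at the last documented date on drug. Report the Kaplan-Meier 1-year discontinuation proportion per cohort and the between-cohort difference with a confidence interval, and state that this assumes uninformative loss.
3. Run the chi-square comparison on all eligible patients under both bounds (all lost counted as discontinued, all lost counted as continuing) and under the two differential extremes between cohorts. Step 5 of the working shows why these must accompany the Kaplan-Meier estimate.
4. Report the number lost in each cohort.

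The 38 per cohort and the 20% allowance stay as they are. The cost is an eligibility amendment after recruitment has begun, a change in which consecutive records enter cohort 2, more chart review there, and somewhat wider intervals. Some patients will also have incomplete 12-month service-use data for the economic evaluation. The change is cheaper now than after leavers have been screened out, when recovering them would mean reviewing the records again.
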